##### Treatment adherence

Treatment adherence questions were developed by Gany et al. Costas-Muniz et al. (2016) to identify barriers to cancer treatment among low-income and immigrant cancer patients. The first question asks if the respondent has missed any of the following appointments in the last three months: chemotherapy/infusion, radiation, general oncology, follow-up, or any other cancer-related appointment. If the respondents indicates yes, they are asked to identify a reason for missing each of the identified appointments: did not have childcare, could not afford transportation to appointment, could not afford copayment, could not afford insurance deductible, was not covered by insurance, prior approval was not obtained, I forgot about my appointment, I was scared/anxious, or other, please describe: (free text). The second question asks if the respondent has missed a dose of cancer-related medication in the last three months and if so, select a reason why: forgot to take it, forgot to buy/pick it up, not covered by insurance, no insurance, could not afford copayment, no time to buy/pick up, do not think they will work/help, do not like the side effects, could not afford transportation to the pharmacy, other, please describe (free text). The outcome variable is binary (yes/no to having missed any appointment or medication dose in the past 12 months).

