### Sample size

The sample size was determined by the amount of philanthropic funding we secured for the Trial which was sufficient to provide $12,000/year to 100 participants. After accounting for anticipated attrition we determined that a 250 person sample was needed – 100 in the intervention group and 150 in the control group (overrecruited for differential attrition). We conducted power analyses based on the literature and pilot study findings to determine detectable treatment effects in the primary outcomes of interest. Power analyses methods and results for each primary outcome are described below. Recruitments sites were selected for serving racially diverse, low-income patient populations. Our pilot study sample was 50% Black, 35% white, 4% Asian, 4% mixed, and 7% other. 52% of the sample identified as Hispanic or Latino.

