### Allocation

Each week participants with completed baseline surveys in Qualtrics will be randomly assigned to one of the study conditions using a computer generated 1:1.5 randomization schedule stratified by age and recruitment site. We will over recruit for the control arm to compensate for an expected 30% differential attrition rate (an estimate derived from yet unpublished U.S. guaranteed income RCTs). Randomization schedule will be stored in a password protected excel spreadsheet that can only be accessed by the principal investigator and senior research coordinator who are not involved in the day-to-day recruitment of participants.

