#### Data management

Completed consent forms will be stored in a private institutional server maintained by the PIs University. Survey data will be entered and stored in Qualtrics, an online data collection and storage platform. The Qualtrics platform provides a high level of data safety and security that is HIPAA compliant for the collection and storage of personally identifiable information (Qualtrics, 2023). During periods of data analysis, data will be exported from Qualtrics to Stata SE17 as a .data file. The data will be stored in and accessed using Box, a secure cloud based platform that conforms to global compliance requirements for data privacy (Box, 2023). To protect confidentiality, we will only collect information from the participants that is essential to the study's aim of understanding the impact of UCTs on cancer patients' health and treatment outcomes. Participant's names, dates of birth, and treatment status will be collected from the electronic medical record for the purposes of outreach prior to the study. The research team will keep this information in a single, password protected excel spreadsheet stored on and accessible through a secure online document sharing platform. This information will be used to contact potential participants over the phone or at their next clinic appointment. We will maintain the contact information of all potential participants even if they decline to participate or are found ineligible in order to conduct feasibility analyses. Participants who enroll will provide identifiable personal information that will be linked to the survey data until data collection and analysis are complete. When the study is complete the data will be de-identified and stored in a secure online database with unique identifiers. The unique identifiers will be linked to the participant's personal information (name, date of birth, contact information) on a single, password protected excel spreadsheet stored on the principal investigator's password protected personal computer. Social Security Numbers (SSN) will be collected at study enrollment and entered directly into a separate, high security server maintained by the PI's University. To protect participants' eligibility for public benefits, each month the PI or Senior Research Coordinator will transfer participant SSNs and trial group allocation directly to SSA through its secure Government to Government Services Online application.

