Linear mixed-models and GEEs were selected because of the longitudinal nature of the study in which repeated measures will be collected across five timepoints. This approach will allow us to integrate observations from all five data collection time points into the statistical models. We plan to adjust these models by accounting for age, gender, race, new or recurrent cancer diagnosis, baseline food security, baseline housing stability, and baseline ECOG. These likely covariates were selected because they represent factors that have been associated with financial toxicity, quality of life and nonadherence in past studies (Altice et al., 2016; Yabroff et al., 2018). We suspect these variables will be correlated with the outcome variables, however, correlation structure will be determined at time of analysis.

Mortality as a long-term exploratory outcome will be analyzed at each time point separately. Chi-square (or, if necessary due to sample size restrictions, Fisher's Exact Tests) will be used to test for differences between the treatment and control groups. Logistic regressions will be used at each time point and will control for age, gender, race, new or recurrent cancer diagnosis, baseline food security, baseline housing stability, and baseline ECOG.

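### The adjustment set omits whether a patient is on systemic therapy or on surveillance: a low-severity gap, mainly for the nonadherence GEE if status-related drop-out differs between arms

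*Protocol article*

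**What the plan says.** Statistical methods adjusts the linear mixed models and GEEs by "accounting for age, gender, race, new or recurrent cancer diagnosis, baseline food security, baseline housing stability, and baseline ECOG". It calls these likely covariates and gives the reason: "These likely covariates were selected because they represent factors that have been associated with financial toxicity, quality of life and nonadherence in past studies".

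Inclusion criteria lists patients receiving chemotherapy or immunotherapy and, as a separate item, patients on surveillance within 12 months of systemic therapy. The lead-in says every item must be met.

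Treatment adherence asks about missed infusion, radiation, oncology and follow-up appointments and about missed cancer medication. The outcome is binary: "yes/no to having missed any appointment or medication dose in the past 12 months". (The items themselves ask about three months; that is a separate matter.)

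Allocation uses a "computer generated 1:1.5 randomization schedule stratified by age and recruitment site" and over-recruits controls for "an expected 30% differential attrition rate". Under Data management, "treatment status will be collected from the electronic medical record for the purposes of outreach prior to the study". Therapy or surveillance status is not a stratification factor. It is also absent from the baseline survey items in Data collection methods and from the baseline characteristics listed in Statistical methods.

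**The concern.** One patient can hardly be on chemotherapy and on post-treatment surveillance at once, so the workable reading is that the two criteria are alternatives and the trial mixes both groups. A patient on surveillance has no infusions to miss and probably fewer doses. Status is therefore tied to a primary outcome by the way that outcome is built, yet it is missing from a list chosen for association with nonadherence, among other outcomes.

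An unweighted GEE on observed data handles outcome-related loss only through the covariates it contains. If patients on therapy drop out more often in one arm than in the other, the responding case mix drifts apart between arms, and a model without status reads that drift as a treatment effect. If it is on-therapy controls who are lost, the remaining controls look more adherent and a benefit is masked.

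**Working it through.** **The plan's own figures.** The protocol gives no figure on this point. As a check that the design is understood, the COST power was recomputed. The protocol gives N = 200, 8% mortality per interval, intraclass correlation 0.6, difference 2.4, SD 7.1 and covariate correlation 0.5 to 0.8. Mean retention over five timepoints is the average of 0.92^0 to 0.92^4, which is 0.852, so effective N = 170.5. The SD becomes 7.1 × sqrt(1 − R²) × sqrt((1 + 4 × 0.6)/5). Power at two-sided 0.05 (assumed) and 1:1 is 0.871 to 0.994, against the stated 0.867 to 0.993. The stated nonadherence power of 0.065 to 0.095 was not reproduced on the same basis (0.137 to 0.239); nothing below rests on it.

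**Inputs for this point.** From the protocol: "100 in the intervention group and 150 in the control group", and 30% differential attrition. Not in the protocol, so assumed: share on therapy p = 50% (30% to 70% for the imbalance check); nonadherence 20% or 30% on therapy against 10% on surveillance (a gap of 10 or 20 points); retention by arm and status.

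**Chance imbalance.** SD of the arm difference in status share = sqrt(p(1 − p)(1/100 + 1/150)).
- p = 0.5: sqrt(0.25 × 0.01667) = 0.0645; 95% range ±12.7 points.
- p = 0.3 or 0.7: sqrt(0.21 × 0.01667) = 0.0592; ±11.6 points.

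Multiplied by the gap, this moves a single estimate by up to 1.2 to 1.3 points (10-point gap) or 2.3 to 2.5 points (20-point gap). The unadjusted standard error of about 4.6 to 5.2 points already contains that variation. In 4,000 simulated null trials per setting (one binary outcome, linear-probability model, robust standard errors, no drop-out), mean bias was about 0 and type I error about 0.05 with or without status. The standard error fell from 4.61 to 4.57 points (10-point gap) and from 5.15 to 5.01 points (20-point gap).

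**Drop-out.** Among those retained, the on-therapy share is p·k/(p·k + 1 − p), where k is retention on therapy divided by retention on surveillance. It depends on k alone, so equal k in both arms gives no shift. Bias = (intervention share − control share) × gap. Retention is shown as on therapy/surveillance, with p = 0.5:

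| Intervention | Control | Shares on therapy | Bias, 10-point gap | Bias, 20-point gap |
|---|---|---|---|---|
| 90/90 | 60/60 | 50.0% v 50.0% | 0 | 0 |
| 80/100 | 60/80 | 44.4% v 42.9% | 0.2 | 0.3 |
| 85/95 | 50/70 | 47.2% v 41.7% | 0.6 | 1.1 |
| 90/90 | 50/70 | 50.0% v 41.7% | 0.8 | 1.7 |
| 90/90 | 40/80 | 50.0% v 33.3% | 1.7 | 3.3 |

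Example, last row: control share = 0.5 × 0.4/(0.5 × 0.4 + 0.5 × 0.8) = 0.333; (0.500 − 0.333) × 20 = 3.3 points.

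Simulating the first, fourth and fifth rows gave mean unadjusted bias close to these values. Type I error without status was about 0.05 in the first row, 0.055 to 0.065 in the fourth, and 0.068 to 0.10 in the fifth. With status in the model, bias was at most about 0.1 points and type I error 0.049 to 0.057.

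**The case against.** Most of the case against acting has force.

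- **The list may not be final.** The covariates are called likely, and an article may leave the final set to an analysis plan that is not shown. That stands. Still, the article prints a specific list with a selection rule, and status plausibly meets that rule.
- **Chance imbalance.** A reader might infer that an uneven on-therapy share biases the result. It does not: randomisation keeps the expected imbalance at zero, and the standard error accounts for it.
- **Attrition.** A reader might infer that the expected differential attrition by itself biases the unadjusted estimate through status. It does so only if the link between status and loss differs between arms. The protocol neither states nor excludes this.
- **Pilot benchmark.** A reader might set the largest bias against the pilot nonadherence difference of 14.7 − 11.5 = 3.2 points and conclude that it could account for all of it. That is not a fair yardstick. The pilot was a pre/post comparison of a 30-day measure that moved against the hypothesis, and the 3.3-point bias needs the most extreme scenario. For adequate power the protocol itself looks to a control rate of at least 32% against 14.7%, a gap of 17.3 points.
- **Existing safeguards.** ECOG and new or recurrent diagnosis may stand in partly for status. The plan compares drop-outs with completers in each arm, examines missingness patterns, and compares imputed with non-imputed results. These help, but the listed characteristics omit status, so the checks as described would not show a status problem.
- **Availability.** Treatment status is taken from the record for outreach and is not defined there as therapy against surveillance. That stands; the field needs defining as an analysis variable.

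**Conclusion.** The point holds as a low-severity, nearly free improvement, chiefly for the nonadherence GEE. Omission costs at most about 3% in standard error (5.15/5.01 = 1.03). A bias of about 0.8 to 3.3 points arises if control loss depends on status while intervention loss does not; it is 0.2 to 1.1 points in the two scenarios where both arms lose more on-therapy patients, and zero if the status pattern of loss is the same in both. With status in the model it is about zero.

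These sizes rest on assumed shares, gaps and retention, on a single-timepoint linear-probability model in place of the planned logit GEE, and on reading the two inclusion criteria as alternatives. Nothing is quantified for COST or SF-36, where the mixed models use earlier outcomes and absorb part of any such loss. The documents therefore do not support a claim that all primary analyses are biased.

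**What to change.** Define status at randomisation (on systemic therapy or on surveillance) and carry it from the eligibility check into the analysis file. Add it as a fixed covariate to the primary models, chiefly the nonadherence GEE, and to the imputation model. Show it in the baseline table and in the comparison of drop-outs with completers by arm, so that an arm-specific pattern would be seen. Settle this before outcomes are compared by arm. Reconcile the lead-in to the inclusion criteria with the two therapy-related items.

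The cost is one degree of freedom and one variable that eligibility screening must establish anyway; no new data collection and no change to randomisation.

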#### Trial design

The GIFT Trial is designed as a randomized, controlled, unblinded, multicenter superiority trial with two parallel groups and a combined primary endpoint of financial toxicity, quality of life, and treatment adherence. Randomization will be performed as block randomization with a 1:1.5 allocation stratified by age and treatment center.

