### Data collection methods

All primary and secondary outcomes are patient-reported and will be collected using an online survey administered at baseline, 3, 6, 9, and 12 months post-enrollment. At baseline, the participants will also answer questions about their age, gender, race, education, cancer type, cancer stage, new or recurrent cancer diagnosis, household income, public benefits utilization, employment status and hours worked per week. At each data collection time point, participants will receive an email or text message with a survey link and directions for completing it. A RA will also call the participant to ask if they would like to complete the survey with them over the phone. Greenphire Clincards will be mailed to the participant's address at the 3-month data collection point and filled with $30 for each survey they complete. For the exploratory outcome of mortality, we have partnered with Social Security Administration who will provide aggregate data on participant mortality, earnings, and disability benefits at 2, 3, and 5 years from study enrollment.

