### Statistical methods

All survey data will be entered into and stored in Qualtrics, then analyzed using StataSE 17 or later, SAS v. 9.4 or later, and/or R v. 4.2.2 or later. The following descriptive statistics will be reported side-by-side for the treatment and control group at baseline: age (mean/SD and % over 64); gender (% per category); race (% per category); cancer type and stage (% per category); new or recurrent cancer diagnosis (% per category); baseline food security (mean/SD); baseline housing stability (% experience homelessness); income (mean/SD in U.S. dollars per year); employment (mean/SD in hours per week); ECOG score (% per category), COST score (mean/SD), treatment nonadherence in last 90 days (% yes). To determine if randomization was balanced Chi-square (or, if necessary due to sample size restrictions, Fisher's Exact Tests) will be used for categorical variables and independent *t*-tests (or, if non-normal, Kruskil-Wallis Tests) will be used at baseline, and between drop-outs and completers in each condition.

Linear mixed models will be used for all primary and secondary continuous outcomes over time. We will assess differences between treatment and control group after controlling for possible confounding variables. General estimating equations (GEE) with a logit link and binary distribution will be used for all binary primary and secondary outcomes over time. We will assess the odds ratio between treatment and control groups after controlling for possible confounding variables. GEEs with a log link and poisson distribution will be used for all non-binary, categorical primary and secondary outcomes over time. We will assess the risk ratio between treatment and control groups after controlling for possibly confounding variables.

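### The exploratory mortality models reuse a covariate list justified for other outcomes and omit cancer stage and type, which the trial already collects; the cost is some power and an attenuated odds ratio

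*Protocol article*

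**What the plan says.** Under Statistical methods, the models for primary and secondary outcomes are to be adjusted for "age, gender, race, new or recurrent cancer diagnosis, baseline food security, baseline housing stability, and baseline ECOG". The reason given is "These likely covariates were selected because they represent factors that have been associated with financial toxicity, quality of life and nonadherence in past studies".

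The mortality analysis at 2, 3 and 5 years begins with a chi-square or Fisher's exact test. After that, "Logistic regressions will be used at each time point and will control for age, gender, race, new or recurrent cancer diagnosis", followed by the same three remaining covariates. No separate reason is given for mortality.

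Stage and type appear elsewhere in the article:

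- Data collection methods lists "cancer type, cancer stage, new or recurrent cancer diagnosis" among the baseline questions, and Table 1 gives survey as the source.
- The baseline table in Statistical methods includes "cancer type and stage (% per category", and baseline variables are tested for balance.
- Trial design states "Randomization will be performed as block randomization with a 1:1.5 allocation stratified by age and treatment center", so neither stage nor type is a stratum.
- Eligibility admits stages 3 and 4 and does not restrict tumour type.

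Data collection methods also says that SSA will provide its mortality data in aggregate form.

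**The concern.** The list rests on "factors that have been associated with financial toxicity, quality of life and nonadherence in past studies". Death is a different outcome, and a list chosen for the first three need not suit it. The study objectives define advanced cancer by stage and ECOG together, yet only ECOG is carried into the models. Balance on stage and type will be tested, but the plan gives no way to act on the result. An imbalance would either stay in the mortality contrast or be adjusted for after the data are seen.

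What is at stake is the efficiency and readability of an exploratory comparison with "100 in the intervention group and 150 in the control group". In a logistic model, leaving out a prognostic covariate moves the treatment odds ratio toward the null and costs power.

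**Working it through.** **1. The plan's own mortality figure.** The power section assumes 8% mortality per three-month interval and 28% dead by 12 months. 1 − 0.92^4 = 0.284, so the figure is reproduced. The document gives no power or sample size for mortality.

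**2. Deaths at the analysis times.** Assumption: 8% per quarter continues beyond 12 months. N = 250. The last two columns divide the rarer outcome by an assumed 11 model parameters (planned list) and an assumed 17 (stage and grouped type added).

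| Year | Proportion dead | Deaths | Survivors | Per parameter, 11 | Per parameter, 17 |
|---|---|---|---|---|---|
| 2 | 1 − 0.92^8 = 0.487 | 122 | 128 | 11.1 | 7.2 |
| 3 | 1 − 0.92^12 = 0.632 | 158 | 92 | 8.4 | 5.4 |
| 5 | 1 − 0.92^20 = 0.811 | 203 | 47 | 4.3 | 2.8 |

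Stage alone adds one parameter. At 5 years that gives 47.2/12 = 3.9 survivors per parameter.

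**3. Chance imbalance in stage.** Assumption: 60% of patients are stage 4. The SD of the arm difference is sqrt(0.6 × 0.4 × (1/100 + 1/150)) = 0.063, or 6.3 points. The chance of a gap above 10 points is 2 × (1 − Φ(0.10/0.063)) = 0.114, about 11%. With 50% at stage 4 the SD is 6.5 points.

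**4. Power with and without stage and type.** Logistic regression was simulated with 100 v 150 patients, about 2,000 runs per setting, two-sided 5%. ECOG, new or recurrent status and age were in both models; the other planned covariates were not simulated. Assumptions absent from the document: 60% stage 4; five equally frequent type groups; conditional treatment odds ratio 0.45; stage log odds ratio 0.3, 0.7 or 1.1, paired with an SD of the type effect of 0.3, 0.6 or 1.0 (weak, moderate, strong).

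| Prognostic strength | 2 years, without → with | Gain (points) | 5 years, without → with | Gain (points) |
|---|---|---|---|---|
| Weak | 0.825 → 0.829 | 0.4 | 0.757 → 0.766 | 0.9 |
| Moderate | 0.758 → 0.798 | 4.0 | 0.668 → 0.698 | 3.0 |
| Strong | 0.644 → 0.756 | 11.2 | 0.566 → 0.639 | 7.3 |

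**5. Where the gain comes from.** At 2 years with moderate strength, the mean log odds ratio goes from −0.74 without to −0.84 with the two factors, and its standard error rises from 0.280 to 0.303. The true value is ln 0.45 = −0.80, so the fuller model slightly overshoots, while the smaller model is attenuated.

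**6. Type I error.** With no treatment effect, rejection rates lie between 4.8% and 6.2% over all settings, with little difference between the models.

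**The case against.** The strongest case against raising this is that it concerns an exploratory outcome. No sample size or power claim rests on it, the unadjusted test comes first, and the change leaves that test as it is. Type I error is not at risk. The power gain depends on an odds ratio of 0.45. Read as a marginal effect, this turns 48.7% mortality (odds 0.949) into odds of 0.427, or 29.9%, which is a very large effect that the document nowhere posits. All of this stands and keeps the point minor.

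Two practical objections also stand. Few survivors at 5 years limit what can be added. Stage and type are self-reported, so misclassification would shrink the gain.

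It might also be said that the article calls the covariates likely, leaving the final list to an analysis plan. That wording belongs to the survey-outcome models. The mortality sentence states what the models will control for.

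A reader might infer more than the documents support:

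- *Precision is lost.* This does not hold for a logistic odds ratio: adjustment raises the standard error. What omission costs is power, through attenuation.
- *Imbalance adds further noise to the arm difference.* The ordinary standard error, sqrt(0.487 × 0.513 × (1/100 + 1/150)) = 6.5 points, already contains it.
- *Stage and type are the main prognostic factors.* The document gives no figures on this. ECOG and new or recurrent status are already in the model, and eligibility leaves stage, like ECOG, only two levels.
- *The SF-36 and HADS models share the defect.* Quality of life is one of the stated grounds for the list, so that argument fails for SF-36, and no loss has been quantified for either scale.

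**Conclusion.** The point holds as a minor one, confined to the exploratory mortality models. Their covariate list is carried over from other outcomes without a reason for mortality. It leaves out two disease factors that are collected, tested for balance and not stratified on. A chance imbalance in either stays unadjusted, the odds ratio is attenuated, and about 0 to 11 points of power are lost. That range rests on the assumed stage share, prognostic strengths, odds ratio of 0.45 and continuing 8% quarterly mortality. The omission does not invalidate the comparison.

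A related conflict has to be settled first. If SSA returns only aggregate mortality, no participant-level logistic regression can be fitted, whatever its covariates. Data collection methods and Statistical methods need to be reconciled.

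**What to change.** In Statistical methods, give mortality its own prespecified covariate set that includes cancer stage (3 v 4). Add cancer type, collapsed in advance to a few groups, at the time points where the count of the rarer outcome allows it. With about 47 survivors at 5 years under the assumption above, stage alone may be all that fits there.

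In the same edit, state how vital status will be obtained. Participant-level status would allow the models as written. If only aggregates are available, request deaths by arm and stage, and replace the logistic model with a Mantel-Haenszel comparison stratified by stage.

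The cost is one degree of freedom for stage and a few for type, with the limits of self-report; no new data are collected. The fallback needs a small change to the data transfer, because Data management describes sending SSA only Social Security numbers and group allocation, and a stage grouping would have to go with them.
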